### Power calculation

The power calculation is based on the estimated maximal number of eligible patients who will be available for the study. In the Netherlands there has been only one major outbreak of Q-fever. Since then, the number of new cases is limited. Furthermore, following the outbreak several studies investigating the symptoms following Q-fever are ongoing which limits the number of eligible patients that will be available to enter the present study. The maximal number of available patients is estimated to be 180, 60 patients for each arm of the study. We assumed a drop-out rate of 20 percent, leaving a sample size for the power calculation of 50 participants per arm. Compared to a *t*-test, using ANCOVA increases statistical power. The sample size of 50 can be divided by a design factor of 0.884 (1–0.34^2^), with 0.34 being the correlation between the CIS fatigue severity at baseline and second assessment [49]. The required effect size was estimated using G-Power 3.1.5. based on a sample size of 56, a power of 0.80 and an alpha of 0.05. The analysis showed that we need to assume a moderate controlled effect size of 0.53 to obtain a power of 0.8 for demonstrating a significant difference between the results in the treatment groups and in the placebo group.

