### Statistical analysis

The primary analysis will be the comparison between the experimental groups (CBT or doxycycline) and the placebo group. ITT will be the basis for all analysis. The primary analysis will be done on the data of completers. Completers are all participants who completed the post intervention measurements. When statistical significant differences are found, a sensitivity analysis will be performed on the basis of different assumptions about the values of missing data. To determine if there is a significant difference between the intervention arm and placebo condition, ANCOVA will be used with the outcome measure on the second assessment as dependent measure, the baseline score as covariate, and condition as fixed factor. A priori contrasts will be defined for the factor condition comparing CBT versus placebo, and comparing doxycycline versus placebo. For the secondary outcome measures, namely psychological distress and functional limitations, the same analysis will be repeated, but with the secondary outcome measures at the second assessment as dependent variable, and the scores at baseline as covariate. In this kind of trials ANCOVA yields greater power than other statistical methods [48]. Statistical significance will be assumed at *p* < 0.05 in all analysis. Data will be presented as quantitative results.

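### A 20% drop-out from 60 per arm leaves 48 completers, not 50, so the detectable effect should read about 0.54 rather than 0.53

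*Protocol article*

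**What the plan says.** All of the figures stand in the protocol article under Power calculation. The number of patients is set by availability: "The maximal number of available patients is estimated to be 180, 60 patients for each arm of the study". The Study population section also plans 60 per arm. Drop-out is then allowed for: "We assumed a drop-out rate of 20 percent, leaving a sample size for the power calculation of 50 participants per arm". Next comes the gain from adjusting for baseline: "The sample size of 50 can be divided by a design factor of 0.884", "with 0.34 being the correlation between the CIS fatigue severity at baseline and second assessment". The software calculation is described as "based on a sample size of 56, a power of 0.80 and an alpha of 0.05", and its result is reported as follows: "The analysis showed that we need to assume a moderate controlled effect size of 0.53 to obtain a power of 0.8".

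The Statistical analysis section adds one relevant fact: "The primary analysis will be done on the data of completers". Drop-out therefore directly reduces the number of patients in the primary comparison.

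**The concern.** The number per arm, the drop-out rate and the number remaining are printed close together and cannot all be true. No other section gives a drop-out rate or a number randomised that would yield 50, and a fuller protocol could not reconcile them either, because the fault lies in the stated figures and not in a missing detail.

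The value 50 is also the input to every later step, so the effective sample size and the detectable effect inherit the discrepancy. With recruitment capped by availability, the detectable effect is the one result that the calculation delivers, and it should follow from the stated assumptions. What is at stake is the accuracy of that statement and of the expected size of the primary analysis set.

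**Working it through.** **Inputs (protocol article, Power calculation):** 60 per arm; drop-out 20%; stated completers 50 per arm; baseline to follow-up correlation 0.34; effective sample size 56 per arm; power 0.80; alpha 0.05. Sidedness is not stated. I take alpha as two-sided because a one-sided 0.05 at 56 per arm gives a detectable effect of 0.47, which does not match the reported 0.53.

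**Step 1: reproduce the protocol's figure from 50 completers.**
- Design factor: 1 − 0.34² = 1 − 0.1156 = 0.8844.
- Effective sample size: 50 / 0.8844 = 56.5, used as 56.
- Detectable effect, normal approximation: d = (1.960 + 0.842) × √(2/n). With n = 56, 2.802 × √(2/56) = 0.529.
- Detectable effect, noncentral t (the usual software method for a two-sample t-test): 0.534.

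Both round to 0.53, so everything after the drop-out step reproduces.

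**Step 2: check the drop-out step.**
- 60 × (1 − 0.20) = 48.
- 1 − 50/60 = 16.7%, the drop-out rate that 50 implies.
- 50 / 0.80 = 62.5, so 63 randomised per arm would be needed to keep 50 at 20% drop-out, which is above the 60 said to be available.
- 60 / 1.20 = 50. The figure may have come from dividing by 1.20 instead of multiplying by 0.80. That origin is an inference, and the finding does not depend on it.

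**Step 3: carry 48 through the same method.**
- Effective sample size: 48 / 0.8844 = 54.3, or 54 if rounded down as the protocol rounds 56.5 to 56.
- Expected completers: 3 × 48 = 144, against 3 × 50 = 150.

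| Effective n per arm | Detectable d, noncentral t | Detectable d, normal | Power at d = 0.53, noncentral t | Power at d = 0.53, normal |
|---|---|---|---|---|
| 56 (protocol) | 0.534 | 0.529 | 79.4% | 80.1% |
| 54.3 (unrounded) | 0.543 | 0.538 | 78.1% | 78.8% |
| 54 (rounded down) | 0.544 | 0.539 | 77.9% | 78.6% |

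**Step 4: check without the effective-n shortcut.** Apply the noncentral t to the completers directly, with the effect divided by √0.8844 and residual degrees of freedom either for two arms (2n − 3) or for all three arms (3n − 4). Power at d = 0.53 is then 79.7% to 79.9% with 50 completers per arm and 78.0% to 78.3% with 48. With the three-arm degrees of freedom the detectable effect is 0.530 and 0.542 respectively. The conclusion is the same.

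**The case against.** The strongest reply is that the slip hardly matters, and on size that is right. The detectable effect moves by about 0.01 and is still moderate, as the protocol describes it. Part of the apparent fall from 80% to 78% is also rounding already present: at exactly 0.53 the protocol's own 56 per arm gives 79.4%, so the drop-out step itself costs about 1.5 points (79.4% to 77.9%).

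Two stronger readings are tempting, and the document supports neither.

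- A reader might infer that the design misses its power target. It has no such target effect. The sample size is fixed by the patients available and 0.53 is solved for, so it is neither a prespecified clinically important difference nor a sizing input. A corrected output is a different number, not a failed requirement.
- A reader might combine this slip with a split of alpha over the two comparisons with placebo and quote a detectable effect of 0.60 and power of 68%. Those values need a two-sided alpha of 0.025, whereas the Statistical analysis section sets 0.05 throughout. They also come almost entirely from that change: at the protocol's 56 per arm, alpha 0.025 already gives 0.589 and 70.2%. Whether the two contrasts need adjustment is a separate question.

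What the reply does not remove is the inconsistency itself. The stated number per arm, drop-out rate and number remaining cannot stand together, and the reported effect size rests on them.

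**Conclusion.** The point holds as a minor internal inconsistency. Under the protocol's own 20% drop-out, 48 patients per arm complete, the effective sample size is about 54, the effect detectable with 80% power is about 0.54, and power at 0.53 is about 78%. The difference from the stated figures is two completers per arm (six in total), about 0.01 in effect size and about 1.5 points of power. It does not show a materially underpowered trial, and it changes neither recruitment nor the planned analysis.

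The result rests on two-sided alpha 0.05, the stated correlation of 0.34, and completers as the primary analysis set. The choice between normal and noncentral t methods, and between 54 and 54.3, does not alter the detectable effect at two decimals.

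**What to change.** Reconcile the figures under Power calculation in one of two ways:

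- Keep the 20% drop-out and restate the chain as 60 × 0.80 = 48 completers per arm (144 in total), 48 / 0.884 giving an effective sample size of 54 per arm, and a detectable effect of 0.54 at 80% power.
- If 50 completers per arm was intended, restate the assumed drop-out as about 17%. The 56 and the 0.53 can then stay.

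The sponsor must say which was meant. In either case, state that alpha is two-sided. The cost is a change of wording and figures only, with no extra patients and no change to the analysis.

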## Discussion

The Qure study will be the first randomized placebo-controlled clinical trial to assess the efficacy of long-term treatment with doxycycline and CBT in adult patients with QFS. A limited amount of previous uncontrolled studies suggest a positive effect of long-term treatment with a tetracycline on performance state. The result of one study shows improvement in symptoms, including fatigue, in all patients after 3 months of treatment. However, not all patients met the current criteria for QFS, whereas 7 patients were PCR positive, meeting the current criteria for chronic Q fever [20]. Furthermore, patients were included with complaints lasting for only 3 months, whereas chances for spontaneous recovery are high in the first 6 months after the initial infection. The other study, primarily focussing on the role of *C. burnetii* in CFS, reports improvement in performance status, a decreased mean headache score, and a decrease in mean weekly temperature after treatment [21]. However, of the 54 patients included, 34 patients were PCR positive at baseline, suggesting chronic Q fever. Furthermore, patients were included with complaints lasting for only 1 month. Therefore, these results cannot be extrapolated, and this long-term treatment is currently not often used in clinical care of patients with QFS. Furthermore, the efficacy of CBT in patients with QFS has not been evaluated in a randomized design. Currently, the decision whether or not to treat is made arbitrarily, as evidence-based strategies are lacking. The Dutch outbreak offers us a great and maybe the only opportunity to conduct research on the best treatment of QFS.

In conclusion, the Qure study will provide greater insight into effectiveness of treatment options for adult patients with QFS. If an effective treatment modality for QFS will be found, significant benefit can be achieved in quality of life, efficiency in treatment and cost-effectiveness. Furthermore, this study will possibly contribute to the establishment of evidence-based guidelines for the treatment of QFS.

## Abbreviations

AF: Alkaline phosphatase;ALT: Alanine aminotransferase;AST: Aspartate aminotransferase;CBT: Cognitive behavioral therapy;CBRSQ: Cognitive behavioral responses to symptoms questionnaire;CDC: Centre for disease control;CFS: Chronic fatigue syndrome;CIS: Checklist individual strength;ECCF: Expert centre for chronic fatigue;GCP: Good clinical practice;GMP: Good manufacturing practice;IMQ: Illness management questionnaire;ITT: Intention to treat;PARS: Physical activity rating scale;RCT: Randomized controlled trial;SCL90: Symptom checklist 90;SES28: Self efficacy scale;SIP: Sickness impact profile (questionnaire);QFS: Q fever fatigue syndrome.
